
#### 2.5.3. Imaging Assessments

Patients will undergo diagnostic imaging (CT of the head, chest and abdomen or PET-CT) up to 4 weeks before the start of treatment, the 12th (+/−2) and 28th (+/−2) weeks after the start of treatment and at the occurrence of the event (in case of suspicion of disease progression, the occurrence of immune-related side effects, deterioration of the condition, etc.).

The response to the treatment will be evaluated radiologically with imaging methods in accordance with the irRECIST criteria (criteria for evaluating the immune response in solid tumors). The irRECIST criteria divide the response to treatment into individual groups: complete response (CR, complete response); partial response (PR, partial response); stagnation (SD, stable disease); and progression (PD, progressive disease). Pseudoprogression is defined as a transient radiological progression of the disease without a clinical picture and a gradual reduction of the burden of the underlying disease.

##### Interim Analysis

An interim analysis of data will be made of the first 20 patients. The results will be used to amend the protocol if necessary.

#### 2.5.4. Statistical Methods

The gastrointestinal microbiome, PD-L1 and Interferon Gamma expression will be correlated with one year of PFS as the primary outcome of the study. An interim analysis will be made after the first 20 included patients.

We will analyze the 16S rRNA sequences with the appropriate software tools from the Mothur software package, and we will perform analysis of molecular variance (AMOVA) and principal coordinate analysis (PCoA). For the statistical analysis of the differences in the representation of the sequences of individual bacterial groups in the studied microbiomes, we will use the DeSeq 2 package from the R programming environment. The association between phylogenetic diversity, taxonomic units, immune cells and the objective response to treatment will be determined using the Wilcoxon test. To compare values at different time points, we will use the paired *t*-test or corresponding non-parametric alternative. When comparing several groups at the same time, we will use the Kruskal–Wallis test. All differences will be considered statistically significant when *p* < 0.05.

The Kaplan–Meier method will be used to calculate survival (PFS), and the survival comparison of multiple groups will be calculated using the log-rank test. The association between the change in PD-L1 or IFNγ expression and response to treatment will be assessed using a logistic regression model and a multivariate model in which different variables will be included. Pearson’s or Spearman’s correlation test will be used to correlate changes in PD-L1 or IFNγ expression levels in tumor and blood.

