## Abstract

Background: Immunotherapy has been successful in treating advanced melanoma, but a large proportion of patients do not respond to the treatment with immune checkpoint inhibitors (ICIs). Preclinical and small cohort studies suggest gastrointestinal microbiome composition and exosomal mRNA expression of PD-L1 and IFNγ from the primary tumor, stool and body fluids as potential biomarkers for response. Methods: Patients treated with immune checkpoint inhibitors as a first line treatment for metastatic melanoma are recruted to this prospective study. Stool samples are submitted before the start of treatment, at the 12th (+/−2) week and 28th (+/−2) week, and at the occurrence of event (suspected disease progression/hyperprogression, immune-related adverse event (irAE), deterioration). Peripheral venous blood samples are taken additionally at the same time points for cytologic and molecular tests. Histological material from the tumor tissue is obtained before the start of immunotherapy treatment. Primary objectives are to determine whether the human gastrointestinal microbiome (bacterial and viral) and the exosomal mRNA expression of PD-L1 and IFNγ and its dynamics predicts the response to treatment with PD-1 and CTLA-4 inhibitors and its association with the occurrence of irAE. The response is evaluated radiologically with imaging methods in accordance with the irRECIST criteria. Conclusions: This is the first study to combine and investigate multiple potential predictive and prognostic biomarkers and their dynamics in first line ICI in metastatic melanoma patients.

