### 2.2. Study Objectives

#### 2.2.1. Primary Objectives

To determine the relationship between the predominant composition of the human gastrointestinal microbiome and the objective response to treatment with ICIs in patients with metastatic malignant melanoma.To determine whether the dynamics of exosomal mRNA expression for PD-L1 and PD-L1 on the surface of immune cells is related to the response to immunotherapy treatment and has predictive value.To determine whether the exosomal mRNA expression for IFNγ is related to the response to immunotherapy treatment and has a predictive value.

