#### 2.2.2. Secondary Objectives

To determine whether a specific composition of the microbiome is associated with the occurrence of immune-related side effects in treatment with ICIS.To determine the effects of ICI on the gut microbiota over different time points.

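### The declared primary outcome, one-year PFS, does not match the three primary objectives, which are all written on response to treatment.

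*Protocol article*

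**What the plan says.** Section 2.5.4 (Statistical Methods) opens with the declaration that the three biomarkers "will be correlated with one year of PFS as the primary outcome of the study".

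The primary objectives in section 2.2.1 are written differently. Objective 1 relates "the predominant composition of the human gastrointestinal microbiome and the objective response to treatment with ICIs". Objective 2 asks whether PD-L1 dynamics "is related to the response to immunotherapy treatment and has predictive value". Objective 3 asks whether "the exosomal mRNA expression for IFNγ is related to the response to immunotherapy treatment and has a predictive value".

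The abstract also frames the primary objectives as prediction of response and adds: "The response is evaluated radiologically with imaging methods in accordance with the irRECIST criteria". Section 2.5.3 repeats irRECIST and lists four categories: CR, PR, SD and PD.

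On irAE, the abstract's sentence on primary objectives includes "its association with the occurrence of irAE". Section 2.2.2 places the corresponding microbiome question among the secondary objectives: "To determine whether a specific composition of the microbiome is associated with the occurrence of immune-related side effects".

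**The concern.** A primary outcome should answer the primary objectives. Here the statistical section names an outcome that the objectives do not use, and the objectives use one that the statistical section does not call primary.

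Two things are at stake. First, response and one-year PFS can disagree for the same patient. If response means CR or PR, a patient with stable disease and no progression at one year is a non-responder but a PFS success; a responder who progresses within the year is the reverse. A biomarker could be associated with one outcome and not the other.

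Second, section 2.5.4 applies p < 0.05 to all differences and names no primary test, so either result could later be presented as the answer to the main question. The plan also has an interim analysis of the first 20 patients whose results may lead to a protocol amendment. If the mismatch is still open then, the choice of primary outcome could be made after outcome data have been seen.

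**Working it through.** The plan states no power, effect size or event count for this point, so there is no figure to reproduce. The check is mainly one of text.

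**Step 1: the outcome named in each place.**

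| Place | Outcome | Status given |
|---|---|---|
| Abstract | Response (irRECIST), plus irAE association | Primary objectives |
| 2.2.1, objective 1 | Objective response | Primary objective |
| 2.2.1, objectives 2 and 3 | Response to immunotherapy | Primary objectives |
| 2.2.2 | Microbiome and irAE | Secondary objective |
| 2.2.3 | Response and progression-free survival, by irAE status | Exploratory objective |
| 2.5.4, opening sentence | One-year PFS | Primary outcome |
| 2.5.4, Wilcoxon test | Objective response | Not ranked |
| 2.5.4, logistic regression | Response | Not ranked |
| 2.5.4, Kaplan–Meier and log-rank | PFS | Not ranked |

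In the objectives, progression-free survival appears only at the exploratory level, and there for a different comparison (patients with and without irAE).

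**Step 2: could response simply mean PFS?** No section defines it so. Section 2.2.3 names better response and longer progression-free survival as two separate things, and section 2.5.4 gives them separate methods.

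**Step 3: does the sample size show which was meant?** Section 2.1 gives 150 patients with no endpoint attached, so it does not.

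**Step 4: how often could the two outcomes disagree? (Illustration.)** Assumed, not from the documents: objective response rate 45% (the Introduction says only that up to 50% respond), stable disease 15–25%, 30–50% of stable-disease patients progression-free at one year, and 10–20% of responders progressing within the year. Response is taken as CR or PR.

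Discordant share = SD share × P(progression-free at one year given SD) + response rate × P(progression within one year given response)

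- Low end: 0.15 × 0.30 + 0.45 × 0.10 = 0.045 + 0.045 = 0.09, and 0.09 × 150 = 13.5, about 14 patients.
- High end: 0.25 × 0.50 + 0.45 × 0.20 = 0.125 + 0.09 = 0.215, and 0.215 × 150 = 32.25, about 32 patients.

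**Step 5: does the choice change what 150 patients can detect? (Illustration.)** Assumed: two-sided 0.05 and 80% power, so the normal quantiles sum to 1.96 + 0.84 = 2.80.

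- Response primary, biomarker compared between responders and non-responders: detectable standardised difference = 2.80 × √(1/n₁ + 1/n₀). At 30% response (45 vs 105) this is 0.50; at 50% (75 vs 75) it is 0.46.
- PFS primary, biomarker split at its median: events D = 150 × (1 − one-year PFS), with one-year PFS assumed at 30–60% and complete follow-up to one year. Detectable HR = exp(2.80 / √(D/4)). With D = 105 this is 1.73; with D = 60 it is 2.06.

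The two choices use different data and have different detectable effects, so the choice matters for the design as well as the wording.

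**The case against.** **Only one endpoint is ever called the primary outcome.** A reader might infer that the plan declares two primary outcomes. It does not. The abstract and 2.2.1 list primary objectives, and only objective 1 says objective response. This stands, and the point is therefore limited to a mismatch between outcome and objectives.

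**Response may be a general concept, with PFS as its measure.** This is possible for objectives 2 and 3 and for the abstract, since irRECIST includes progression and section 2.3.6 gives 12 months of follow-up. It cannot cover objective 1, and 2.2.3 and 2.5.4 keep the two outcomes apart. The reading narrows the conflict but does not remove it.

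**An unseen SAP or full protocol may settle it.** The article does not leave the matter open. It fixes it in two incompatible ways, so a SAP could follow one statement only by departing from the other.

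**A false-positive rate.** A reader might multiply three biomarkers by two outcomes and infer a rate of 1 − 0.95⁶ = 26%. The documents do not support that as a measure of this defect. It assumes six independent tests, yet response and PFS come from the same patients and largely the same scans. Three biomarkers on a single outcome already give 1 − 0.95³ = 14% under independence, so about half would remain after the fix. The microbiome is also more than one test in 2.5.4. Multiplicity is a separate matter.

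**Which outcome was intended.** A reader might infer that irRECIST response was really meant, because the objectives and scheduled scans fit it. But PFS is the only declared primary outcome, and the 12-month follow-up fits it equally well. No dichotomy such as CR+PR versus SD+PD appears anywhere in the article. The documents do not decide this.

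**Conclusion.** The point holds as an internal inconsistency in the current text: section 2.5.4 makes one-year PFS primary for all three biomarkers, while the abstract and section 2.2.1 make response the primary question. No reading of the article reconciles them fully. It should be corrected because the plan does not determine which result answers the main question.

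This conclusion rests on the wording alone. The discordance of 9–22% and the detectable effects depend on assumed rates, power and sidedness; they show that the choice is not cosmetic but are not estimates for this cohort. The documents give no sign that results have been or will be chosen selectively; the plan merely leaves room for it.

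The irAE mismatch between the abstract and 2.2.2 is a smaller inconsistency, with no bearing on response versus PFS.

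**What to change.** Name one primary outcome with its time point, use it in the abstract, 2.2.1 and 2.5.4, and list the other as secondary. Either route is acceptable:

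- keep one-year PFS as primary and reword the three primary objectives and the abstract to match; or
- make irRECIST objective response primary, state the dichotomy and the assessment time, and amend 2.5.4.

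In 2.5.4, mark which test on the chosen outcome is the primary analysis for each biomarker. Make the choice without reference to outcome data, including the 20-patient interim analysis, and record this in the amendment. The documents do not say whether that analysis has taken place; if it has, the amendment should say so. List the irAE association at the same level in the abstract and in 2.2.2.

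The cost is a documented protocol amendment within the recruitment period (October 2022 to October 2025), and one outcome loses or forgoes primary status. No additional patients, samples or scans are required by the realignment itself. The second route replaces the only declared primary outcome, so it is a substantive change and should be justified as one.

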## 2. Methods and Design

### 2.1. Study Design

The study is cohort-prospective, non-randomized and non-interventional (Figure 1). It will assess the association between the predominant composition of the human gut microbiome and the response to immunotherapy treatment with PD-1 and CTLA-4 inhibitors in metastatic malignant melanoma. It will also observe whether specific biomarkers (host immune cells population, PD-L1 and IFNγ expression) correlate with the predominant composition of the gut microbiome and the response to treatment with immunotherapy.

Patients with metastatic malignant melanoma who will be treated with immunotherapy in the first line in the three-year period from October 2022 to October 2025 will be included in the research. One-hundred-and-fifty patients will be included. Consenting patients will be asked to provide clinical data and donate biological samples before, during and after completing their treatment. Patient data will be anonymized—date of birth, gender, date of diagnosis, performance status at initiation of treatment, liver enzymes, tumor markers—LDH, S100, localization, BRAF status, treatment type, response to immunotherapy, treatment time, immune-related adverse events of treatment.

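### AMOVA, the only whole-community test named, does not separate a shift in microbiome composition from a difference in between-patient spread, and unequal outcome groups make this matter

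*Protocol article*

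**What the plan says.** The first primary objective (2.2.1) is "To determine the relationship between the predominant composition of the human gastrointestinal microbiome and the objective response to treatment with ICIs". The first secondary objective (2.2.2) is "To determine whether a specific composition of the microbiome is associated with the occurrence of immune-related side effects". Both concern the composition of the community.

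For the 16S sequences, section 2.5.4 states "we will perform analysis of molecular variance (AMOVA) and principal coordinate analysis (PCoA". PCoA is an ordination, not a test. For individual bacterial groups, "we will use the DeSeq 2 package from the R programming environment". A further sentence covers univariate quantities: "The association between phylogenetic diversity, taxonomic units, immune cells and the objective response to treatment will be determined using the Wilcoxon test". The threshold is common to all of them: "All differences will be considered statistically significant when *p* < 0.05".

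AMOVA is therefore the only named test that looks at the community as a whole. The section does not give its distance, the groups it compares, how a significant result will be worded, or any accompanying test of spread.

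On size, section 2.1 states "One-hundred-and-fifty patients will be included" and describes a non-randomized cohort.

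**The concern.** AMOVA asks whether patients in different groups lie further apart than patients in the same group. Two situations can make the answer yes: the groups have different typical communities, or one group is more heterogeneous from patient to patient. The objectives ask only about the first.

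Group sizes are set by outcome, so balance is not controlled. Unequal size combined with unequal spread is where a permutation test of this kind departs from its nominal level. In one direction, heterogeneity could be read as a favourable or unfavourable composition. In the other, a real difference could be missed. The Discussion envisages that patients with an unfavourable composition might in some cases be steered to other first-line drugs, so the reading of this result matters.

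**Working it through.** The article gives no power, effect size or error rate for AMOVA, so there is no stated figure to reproduce.

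**Inputs from the article**
- N = 150 (2.1); threshold 0.05 (2.5.4).
- Response: the Introduction says up to 50% respond, so at most 75 of 150.
- irAE: section 1.1 says more than a third, so about 150 / 3 = 50 against 100 at exactly one third. These are background statements, not design inputs.

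**Assumed inputs**
- Distance: Euclidean or Bray-Curtis.
- Ratio of between-patient SDs: 1, 1.25, 1.5 or 2.
- 40 dimensions for the main Euclidean and Bray-Curtis runs.

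**Statistic.** With squared distances d², SST = Σd²/N over all pairs, SSW = the sum over groups of (Σd² within the group)/n, and SSB = SST − SSW. For two groups, F = SSB / [SSW/(N − 2)]. The p-value comes from permuting labels (299 permutations).

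**Why group size matters.** Take Euclidean distances, a common centroid and per-dimension variances s₁² and s₂². The expected mean squares per dimension are:

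- between: (n₂s₁² + n₁s₂²)/N
- within: [(n₁ − 1)s₁² + (n₂ − 1)s₂²]/(N − 2)

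Put s₁ = 1.5 and s₂ = 1:

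- 75:75: between (75×2.25 + 75)/150 = 1.625; within (74×2.25 + 74)/148 = 1.625; ratio 1.00.
- 50:100 (smaller group more spread): between (100×2.25 + 50)/150 = 1.833; within (49×2.25 + 99)/148 = 1.414; ratio 1.30.
- 100:50 (larger group more spread): between (50×2.25 + 100)/150 = 1.417; within (99×2.25 + 49)/148 = 1.836; ratio 0.77.

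The permutation reference is centred near 1. The test is therefore roughly exact in the first case, liberal in the second and conservative in the third.

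**Simulated rejection rates, Euclidean, equal centroids** (first group more spread; 600 to 1500 replicates)

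| Split | SD ratio 1 | SD ratio 1.5 | SD ratio 2 |
|---|---|---|---|
| 75:75 | 4.5% | 4.6% | 4.5% |
| 68:82 | – | 9.1% | – |
| 60:90 | – | 18.8% | – |
| 50:100 | 5.8% | 32% | 59% |
| 90:60 | – | 0.7% | – |
| 100:50 | 4.7% | 0.1% | 0% |

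Separate Euclidean runs at 50:100 gave 13% to 26% for SD ratios of 1.25 to 1.5, and 0% to 0.3% with the spread reversed. Taken together, the liberal case is about 13% to 32%.

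**Bray-Curtis, identical mean taxon proportions, spread varied through the Dirichlet concentration**
- Equal spread: about 4%.
- SD ratio about 1.5: 95% at 75:75, 95% at 50:100, 67% at 100:50, 16% at 120:30.
- Milder case (80 taxa), mean distance to centroid about 12% larger in the first group: 34% at 75:75, 45% at 50:100, 21% at 100:50.

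**Are the Bray-Curtis cases pure spread?** No. At 75:75 with concentrations 13 and 20, AMOVA rejected in 50% of trials. Mean Shannon diversity was 2.61 against 2.84, and a Wilcoxon test on it was significant in 99.5%. The squared distance between centroids was about 0.002, against 0.0001 with equal concentrations. The groups differ in location in the tested space as well as in spread.

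**Does a dispersion test detect the problem?** On Euclidean distances at SD ratio 1.5, a Bartlett-type permutation test of spread (HOMOVA style) flagged the difference in 100% of trials at 75:75, 50:100 and 100:50. With equal spreads it flagged 4% to 6%.

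**The case against.** The strongest reply is that a condensed article commonly leaves a companion diagnostic to the full protocol or SAP. That stands as far as it goes: the absence of a dispersion test is not in itself an error, and nothing here is contradicted. The point rests on the test and threshold the article does name, and on how its result can be read.

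Three stronger readings are tempting, and the documents do not support them.

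- *AMOVA rejects whenever spread differs.* It does not. With a common centroid and equal groups it holds about 5%, and it is conservative when the larger group is more spread. A response share near 50% would leave the primary contrast close to balanced and little affected on Euclidean distances.
- *The high Bray-Curtis rates in equal groups show false findings of composition.* The article names no distance, and those cases also shift the centroid and within-patient diversity. Mean taxon proportions are equal, so a reader could still be misled, but the rates cannot be attributed to spread alone.
- *A spread difference will be reported as a composition difference.* Section 2.5.4 fixes no wording. PCoA, DESeq2 and the Wilcoxon tests on diversity and taxonomic units sit beside AMOVA, and an overall AMOVA p-value cannot name a favourable taxon.

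These cross-checks help, but none of them formally tests spread.

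**Conclusion.** The point holds as a caution on interpretation with a definite remedy. A significant AMOVA could be misread as a difference in predominant composition, chiefly where outcome groups are unequal. At 50:100 on Euclidean distances with an SD ratio of 1.25 to 1.5, rejection is about 13% to 32% if the smaller group is more spread and near 0% if the larger group is. At equal sizes it stays at about 5%. On Bray-Curtis distances unequal heterogeneity raises rejection even in equal groups, and at 100:50 and 120:30 the SD-ratio-1.5 runs still over-rejected, so the conservative direction is a Euclidean result.

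The distance, the contrasts, the dimension, the spread ratios and which group is more spread are all assumed. The irAE share is background from section 1.1, and a share nearer one half would reduce the Euclidean effect.

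**What to change.** In 2.5.4, for each AMOVA contrast (response groups, irAE groups), run and report a homogeneity-of-dispersion test (HOMOVA or PERMDISP) on the same distance matrix. Where spread differs, do not attribute a significant AMOVA to composition alone. Interpret it together with the dispersion result, the PCoA plot, the diversity comparison and the taxon-level tests.

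Do not use the dispersion test as an all-or-nothing gate. It detects spread differences readily, so a gate would relabel genuine composition shifts as variability whenever spread also differs.

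The cost is one extra test per contrast on a matrix already computed, a sentence or two of text, and more cautious wording of some results.

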#### 2.3.6. Assessments during the Study

Patients will be followed up at their routine visits at the clinic. The follow-up will be scheduled at 3- or 4-week intervals, depending on the ICIs treatment regimen, when routine examination and laboratory test will be taken. Study-specific data will be collected at three different time points: up to 4 weeks before the start of treatment, at the 12th (+/−2 weeks) and 28th week (+/−2 weeks). Study-specific data will be taken additionally, if suspected disease progression and the appearance of immune-related adverse events or if indicated by the oncologist (Table 1).

Patients will be followed up regularly for the time of the treatment for the first 12 months. The study will be prematurely terminated in an event occurrence defined as disease progression/hyperprogression; by the physician’s choice in severe immune-related adverse events; when high doses of systemic corticosteroid (dexamethasone 4 mg/day or equivalent or higher) or prolonged antibiotic treatment are present; or by the patient’s choice. Before each stool sample donation, the patient will fulfill a questionnaire regarding eating habits, alcohol and tobacco consumption and medications. In the case of antibiotic treatment, the stool sample will be donated after 3 weeks of the last antibiotic dose taken.

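### Paired tests between time points use patients selected partly by outcome, so the estimated change can be biased; a repeated-measures model should sit beside them and the result be called change during treatment

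*Protocol article*

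**What the plan says.** All references are to the protocol article.

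- **Test.** In section 2.5.4 the sentence opening "To compare values at different time points, we will use the paired" goes on to name the *t*-test or a non-parametric counterpart. It is the only method the section assigns to comparing time points. The threshold follows: "All differences will be considered statistically significant when" p is below 0.05.
- **Samples.** Section 2.3.6: "Study-specific data will be collected at three different time points", namely within 4 weeks before treatment, at week 12 and at week 28 (each of the last two ±2 weeks). Sections 2.3.6, 2.3.7, 2.4.1 and 2.4.3 add samples at suspected progression and at immune-related events. Section 2.5.4 gives these no role in the time-point comparison.
- **Exit.** Section 2.3.6: "The study will be prematurely terminated in an event occurrence defined as disease progression/hyperprogression". It also lists severe immune-related events (physician's choice), high-dose corticosteroids, prolonged antibiotics and the patient's choice. I read this as ending the individual's participation.
- **Covariates.** Before each stool sample "the patient will fulfill a questionnaire regarding eating habits, alcohol and tobacco consumption and medications".
- **Objective and design.** Section 2.2.2: "To determine the effects of ICI on the gut microbiota over different time points". Section 2.1: "The study is cohort-prospective, non-randomized and non-interventional" and "One-hundred-and-fifty patients will be included". No untreated comparator is described.

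**The concern.** A pair needs both values from the same patient. The baseline-to-week-28 pair exists only for patients who have not left through progression, toxicity, steroids or antibiotics.

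That selection does harm only if exit is linked to the marker, and such a link is what the study sets out to find: sections 1.2.6 and 2.2.1 expect microbiome composition and marker dynamics to go with response. Two routes matter:

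- If exit depends on the baseline value, those who stay have atypical baselines and regress toward the mean.
- If exit depends on the change itself, those who stay over-represent one direction of change.

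In either case a cohort with no average change can appear to change, and section 2.2.2 would report this as an effect of ICI.

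**Working it through.** **What can be reproduced.** The planned 150 patients come with no effect size, power or dropout rate, and the time-point comparison has no stated figure. The sizes below are therefore illustrations.

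**Inputs.** From the article: N = 150, three scheduled visits, p < 0.05 (taken as two-sided), and a response rate of up to 50% (section 1, set to 50%). Assumed: SD 1, within-patient correlation 0.6, true mean change 0, and exit by week 12/week 28 of 15%/30% or 25%/45%.

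**Pairs left.** Week 12: 150 × 0.85 ≈ 127 or 150 × 0.75 ≈ 112. Week 28: 150 × 0.70 = 105 or 150 × 0.55 ≈ 82.

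**Hand check, outcome-driven exit.** Suppose responders change by +0.25 SD and non-responders by −0.25 SD, and only non-responders leave.

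- 30% exit: stayers are 0.50 responders and 0.20 non-responders. Mean change = (0.50 × 0.25 − 0.20 × 0.25)/0.70 = 0.107 SD.
- 45% exit: (0.50 × 0.25 − 0.05 × 0.25)/0.55 = 0.205 SD.
- Variance of a difference = 2(1 − 0.6) = 0.80, plus the mixture term 0.5² × p(1 − p), where p is the responder share of stayers.
- 30% exit: p = 0.714, variance 0.851, SE = √(0.851/105) = 0.090, shift 0.107/0.090 = 1.19 SE, rejection probability about 21%.
- 45% exit: p = 0.909, variance 0.821, SE = √(0.821/82) = 0.100, shift 2.04 SE, rejection probability about 52%.

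The simulation (2,000 cohorts per setting) gave 0.105 and 0.205 SD, with 21% and 54%.

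**Hand check, exit on baseline.** Expected change given baseline y₀ is −(1 − 0.6)y₀ = −0.4y₀. The simulated biases of −0.106 and −0.169 SD mean that stayers' baselines average 0.106/0.4 = 0.27 and 0.169/0.4 = 0.42 SD above the cohort.

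**Simulated week-28 results** (true change 0; ranges cover the two exit scenarios; the model is a maximum-likelihood repeated-measures model on scheduled samples)

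| Exit depends on | Paired bias (SD) | Paired false positives | Model bias (SD) |
|---|---|---|---|
| Baseline value | −0.11 to −0.17 | 25–40% | about 0 |
| Baseline before week 12, then week-12 value | −0.05 to −0.07 | 10–12% | about 0 |
| Outcome, change differs by outcome | +0.11 to +0.21 | 21–54% | +0.08 to +0.16 |
| Outcome, change unrelated to it (25%/45% only) | 0.00 | about 4% | 0.00 |

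Two further sets of runs, also with N = 150 and correlation 0.6, let about half leave before week 28:

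- Exit on week-12 change (logistic slope 0.5 or 1.0; compound-symmetric or AR(1) correlation): paired bias 0.09 to 0.28 SD, false positives 16–58%, likelihood bias under 0.01 SD. With exit on the week-12 level alone, both methods were unbiased.
- Exit on a stable latent patient level (slope 0.5, 1.0, 2.0): paired bias 0.00, false positives 4–7%; likelihood bias −0.04, −0.10, −0.17 SD.

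**How much the model recovers** in the third table row. Scheduled samples only: 1 − 0.078/0.105 = 26% and 1 − 0.157/0.205 = 23% of the bias removed. With each leaver's exit sample used as that visit's value: residual 0.024 and 0.048 SD, so 77% removed in both scenarios. This is idealised, because it assumes every leaver gives an exit sample.

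**The case against.** The strongest reply is that the paired test is sometimes the safer method. A within-patient difference cancels a stable trait. If exit depends on a stable microbiome type that is only measured with noise, which is close to the article's own rationale, the paired test is unbiased and the likelihood model is not. This stands, and it rules out replacing one method with the other. A reader might infer that the mixed model makes the weaker assumption or corrects the problem; the latent-level and outcome-driven results show that neither is so in general.

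Other replies:

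- *Leavers are not wholly lost.* This stands. Week-12 pairs include everyone who leaves later, and event samples can give a baseline-to-event pair. But those samples are not at the scheduled week, are taken because of the outcome, and have no stated place in the comparison.
- *The primary objectives are analysed otherwise.* This largely stands. A reader might infer that the PD-L1 and IFNγ dynamics objectives fall with the paired test, but section 2.5.4 relates their change to response by logistic regression. Microbial composition also has AMOVA, PCoA and DESeq2, which a linear mixed model does not replace.
- *Change among patients still on study is a legitimate target.* This stands if the report says so.
- *Missing-data handling belongs in the SAP.* An absent covariate list or missing-data section is no finding. The point rests on what is stated: a named test, an outcome-linked exit rule, and an objective worded as a treatment effect.

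**Conclusion.** The concern holds in conditional form. The planned pairs are selected partly on outcome, and the week-28 change can be biased when exit is related to a marker's baseline value or its change. The illustrative size is about 0.1 to 0.3 SD, with false-positive rates between roughly 15% and 58% where that link runs throughout, and 10–12% in the milder mixed setting. These figures rest on assumed exit rates, correlation and exit mechanisms, none of which the article gives.

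A reader might infer that the paired result *is* biased. The article does not support that: it shows no link between marker and exit, and where change is unrelated to exit the paired test keeps close to its nominal level.

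The main exposure is the secondary objective in section 2.2.2. Separately from any bias, a before-after change without a comparator mixes ICI with diet, antibiotics, steroids and time, and neither method makes it an effect of ICI. The change is worth making but is not a fatal flaw.

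**What to change.** 1. For continuous markers (diversity, immune-cell percentages, expression; transformed where needed), add to section 2.5.4 a linear mixed model for repeated measures. Use all baseline, week-12, week-28 and event-triggered samples, with actual sampling time, event type, and the recorded antibiotic, steroid, diet and regimen data as terms.
2. Keep the paired test and report both, stating each assumption: the model needs exit to be explained by observed data; the paired test needs exit to be unrelated to change. Where they disagree, say so and do not choose after the fact.
3. State that the paired result describes patients still on study at that visit, and give the number of pairs and the reasons for exit.
4. Treat any response-by-week-28 interaction cautiously, because progression ends participation and few progressors will remain.
5. Reword the objective in section 2.2.2 as *change in the gut microbiota during ICI treatment*.

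The cost is analysis work and a wording change, with no new patients, samples or visits. The downside is reliance on missing at random, which reduces the bias but does not guarantee its removal.
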